## Abstract

**Background:**

Different studies have investigated the effects that changes in drug appearance have on the control of chronic diseases and drug safety. The main objective of the proposed study is to evaluate if changes in the appearance of the packaging and presentation of drugs having the same active ingredient are related to a decrease in adherence and an increase in usage errors for chronic treatment using antihypertensive (enalapril and amlodipine) and hypolipidemic agents (simvastatin) in patients ≥65 years old, over a one-year follow-up period.

**Methods/Design:**

We propose a multicentric observational longitudinal cohort study with a one-year follow-up period in 8 primary health care centers (PHCC) in the Community of Madrid. 259 patients who are ≥65 years old, hypertensive and/or dyslipidemic, undergoing treatment with enalapril and/or amlodipine and/or simvastatin, and under formal follow-up of chronic patients in primary health care will be selected by simple random sampling. The main outcome variable will be a final combined variable (adherence and medication usage errors). Other included variables will be: sociodemographic and clinical variables of the patient, degree of disease control, drug taken, number of changes in the appearance of each drug by the pharmacy, and the type and frequency of both avoidable and non-avoidable adverse effects during the follow-up period. A descriptive and a multivariate analysis of the variables will be carried out by means of a logistic regression model, using the final combined variable as the dependent variable (error and/or inadequate usage of the drug), and variables shown to be related to it during the bivariate analysis as the independent variables.

**Discussion:**

For drugs of the same active ingredient, the effect that different package appearances and presentation may have on the safety of patients undergoing chronic treatments is unknown under the new legislative framework. There are various initiatives that promote the iso-appearance of drugs: “If they are the same, make them look the same”. It is to be expected that older, multi-medicated patients with chronic pathologies will be the ones under a greater risk of suffering from this problem.

## Background

In 2010 the Spanish National Health System (NHS) paid for 958 million prescriptions according to data from a report by the Spanish Society of Public Health and Health Administration. Due to this massive exposure of the population to drugs, and to a non-negligible percentage of patients who suffer avoidable adverse effects, the risks associated with drug usage acquire an enormous relevance from the public health perspective [1].

In 2011–2012, legislative changes have been introduced in order to lower the pharmaceutical expenses in the NHS that affect drug prescription. The Spanish law Real Decreto-ley 9/2011, from August 19 [2], requires the medical prescription to be made according to active ingredient, official Spanish denomination, or common international denomination. This way, homogeneous groupings are established for the same active ingredient in order to facilitate the interchangeability of drugs. Later, the Real Decreto-ley 16/2012, from April 20, which addresses urgent measures to ensure the sustainability of the NHS [3], requires dispensing the lowest priced drug out of all the pharmaceutical bio-equivalent presentations, among other measures.

Since the entry of these laws into effect, the doctor writes the prescription according to the active ingredient, with some exceptions (therapeutic needs and lower cost), and the final choice for the commercial brand is determined by the pharmacy based on the lowest-cost criteria. Therefore, the pharmacy can make the necessary changes in order to adjust to the economic criteria.

In this new legal framework, the patient can receive multiple presentations of the same drug when periodically renewing a chronic treatment using the same active ingredient, with different shapes, colors, and sizes of pills, excipients, and packages.

Without doubting the proven clinical efficacy of generic drugs or prescription by active ingredient, this situation generates worries in the medical field about the fact that these different presentations of the same active ingredient may increase the risk of drug usage errors in chronic treatments, since multiple changes of commercial brands can be made at the pharmacy [2], which may increase the risk of drug usage errors by patients. According to data from the APEAS study [4], which employed an observational design to study the safety of patients in primary care during standard clinical practice, examining over 96,000 consultations in the country during 2007, the prevalence of errors is estimated to be around 1.01%, with an emphasis on the fact that in 48.2% of the cases the causes were related to medication.

Various authors and organizations have developed recommendations for alerting of this problem [5,6]. The US Institute for Safe Medication Practices (ISMP) recommends generic drugs keep the same appearance as the original brand, or a standard universal labeling be used for bio-equivalent medications. This Institute has a National Program of Medication Errors Notification in Spain (ISMP-España), where errors of mistaking different drugs with similar packages have been recorded, as happened with Renitec® 5 mg and 20 mg and Zocor® 10 mg and 20 mg because of having similar packaging. In Spain, various scientific societies (Spanish Society of Family and Community Medicine, Spanish Federation of Community Nursery, and Spanish Society of Attending Quality) have signed a manifesto under the motto “If they are the same, make them look the same”, demanding actions so that packages of drugs containing the same active ingredient show a common appearance, which has been denominated “iso-appearance” [7].

Different studies have investigated the effects that changes in the appearance of drugs (package, shape, size, color) have on the control of chronic diseases. Of particular relevance is a systematic review by De Craen *et al*. [8], published in British Medical Journal, including 6 clinical trials that evaluated the effect of the color of pharmaceutical drug presentations on various factors, for example relating the drug color to a stimulating or depressive effect on the nervous system, or to the location of the effect. In addition to the placebo effect that different drug colors produce, color changes can confuse the patient, increasing the risk of errors. On the other hand, the change that happens at the pharmacies when dispensing medication with a different look may also affect the clinical control of the disease. The effects of drug appearance changes are centered on 2 mechanisms: medication errors (mistaking drugs, duplicating doses) and lack of adherence to treatment (either due to or independent of medication errors).

Undoubtedly, the most vulnerable population to these possible mistakes is the older, multi-medicated population. The changes in pharmaceutical presentations may mean an extra difficulty since they often suffer from visual deficiencies, and even cognitive ones, which can increase the risk of mistakes [9]. All this can generate confusion, forgetfulness, or duplication of dosages, which worsens adherence to the treatment, and therefore endangers their safety and even disease control [10]. The Spanish Ministry of Health, Social Services, and Equality itself establishes the investigation of the safety of medical treatments in the >65-year-old population as a strategic research line [11].

Lack of adherence to treatment is a problem of great relevance [12]. In the 2003 Geneva convention [13], the World Health Organization (WHO) already warned that only half of chronic treatments are followed correctly, and that adherence to them is an important modifier of the effectiveness of health systems. Among the causes for the lack of success of chronic treatments, the WHO refers to economical and social factors, the medical team assisting the patient, the health system, the characteristics of the disease, the treatment itself, and factors related to the patient. However, there are no studies that have evaluated the effect that repeated presentation changes may have on treatment adherence. Strategies have been proposed to avoid changes in commercial presentation, some of which imply manufacturing drugs with specific shapes (for example, the famous blue diamond of Viagra©), while others suggest directly advertising the specific look of the pill [14].

Hypertension (HTN) and dyslipidemia are two very prevalent chronic pathologies in our environment. The prevalence of HTN in Spain is estimated to be around 35%, and almost doubles in patients over 65 years old (68%); as for hypercholesterolemia, it is around 50% when considering levels of total high cholesterol (HDL > 200 mg/dL or people under pharmacological treatment), or 44% if considering high levels of low density lipoproteins (LDL > 130 mg/dL or under pharmacological treatment) [15]. The 3 most prescribed drugs for these pathologies (enalapril, amlodipine, simvastatin) have been selected for this study, which have a high impact on the NHS due to the volume of prescriptions and the high number of patients who chronically consume them, according to data provided to the study auhors, by the NHS. The possibility of repeated changes at pharmacies for this group of drugs can be high; in the Spanish pharmaceutical market, there are currently 45 different presentations of enalapril 20 mg, 40 presentations of amlodipine 10 mg, and 47 presentations of simvastatin 20 mg [16].

In primary health care, we find ourselves in a suitable framework to be able to observe under conditions of standard clinical practice the real effect of these legislative changes on patients with chronic diseases. The formal follow-up of these patients in primary health care will allow us to study the possible effects that appearance changes may have on adherence, possible usage errors, and clinical control of the disease.

### Aim

The main aim of this study is to evaluate if changes of drugs with different package and/or presentation appearance for the same active ingredient are related to a decrease in adherence and an increase in usage errors, in patients ≥65 years old, undergoing chronic treatment with antihypertensives (enalapril and/or amlodipine) and hypolipidemic agents (simvastatin), over a one-year follow-up period.

The secondary objectives are: to describe the number of drug changes made at pharmacies, estimate the frequency of avoidable and non-avoidable adverse effects during the follow-up period, describe the tolerance of patients to the dispensed drugs, and study if the number of changes is related to a decrease in the degree of control of blood pressure (BP) and/or LDL cholesterol.

## Methods/design

### Design

Observational longitudinal cohort study with a one-year follow-up period.

### Scope

The study includes patients from 8 primary health care centers (PHCC) from the Community of Madrid: 2 urban ones (PHCC Avenida de Aragón, PHCC Benita de Avila), 3 suburban ones (PHCC Alameda de Osuna, PHCC El Puerto, PHCC Jaime Vera), and 3 rural ones (PHCC Paracuellos de Jarama, PHCC Las Matas, PHCC Fronteras), which attend a total population of approximately 205,000.

### Patients

All patients who are over 65 years old, diagnosed with HTN and/or hypercholesterolemia, and included in a program for following-up chronic patients in PHCCs will be included. The patient must be under treatment with at least one of the following drugs: enalapril, amlodipine, and simvastatin, with a stable dose during the previous 3 months, and must give informed, written consent.

The criteria for exclusion are: having difficulty to properly understand written or spoken Spanish, foreseeing an address change and not being ascribed to the PHCC for the following year, and suffering from severe systemic disease or other limitations that prevent the patient from attending the PHCC for the follow-up visits.

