### Sample size

Sample size has been calculated to estimate a proportions difference in the degree of adherence to the treatment of 20% between the exposed group (drug changes at the pharmacy) and the non-exposed group. It is estimated that adherence to treatments in the population undergoing chronic treatment is 50%, and the odds ratio (OR) of suffering an event of adherence decrease is double in the group exposed to drug changes (OR = 2) versus the non-exposed one.

For an alpha error of 0.05 and a beta error of 0.20, 237 patients would be necessary. Taking into account the effect of the doctor on adherence of their patients to treatment, it is considered that the outcome of each patient is not independent from other patients from the same cluster, so it is necessary to adjust the sample size because of the design effect. Considering that the number of included patients per doctor is 15, and assuming an intraclass correlation coefficient of 0.01 [17], the required sample size would be 240. If we estimate a 7% loss of patients to follow-up within a one-year period, the final sample size will be 259 patients.

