### Sampling

Random sampling will be performed out of the list of patients who fit the selection criteria (≥65 years old, HTN and/or dyslipidemia, and treated with any of the 3 studied drugs) from each of the 30 participating doctors. Randomization will be performed by an independent researcher using computer software to create the randomization sequence (Excel 2007).

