### Secondary outcome variables

#### Sociodemographic

Age, sex, level of education (illiterate, without studies, primary studies, secondary studies, superior education), and PHCC.

Related to the prescription and active ingredient:Prescribed active ingredient: enalapril, amlodipine, or simvastatin.Change of drug presentation at the pharmacy (Yes/No).Number of changes per drug.Suffering an adverse reaction to the drug (Yes/No), interruption of medication (Yes/No), and the reason for such interruption.Number of avoidable and non-avoidable adverse effects during the follow-up period.Tolerance of the patients to the dispensed drugs according to their own direct statement.

Clinical and analytical:Years of development of HTN and/or dyslipidemia. Presence of pathologies that modify the HTN (nephropathologies, sleep apnea, obesity, and malnutrition). Presence of pathologies that modify the lipid profile (hyperthyroidism, hypothyroidism, obesity, and malnutrition). Comorbidity (cardiovascular pathology, neurological pathology).Treatments that modify BP and the lipid profile (diuretics, alpha and beta blockers), anti-inflammatories, antidepressants and anxiolytics, thyroxin, hormone replacement therapy. Other concomitant treatments.Figures of systolic blood pressure (SBP) and diastolic blood pressure (DBP) in each visit. Difference of SBP and DBP between the first visit and the last recorded data. Percentage of patients with good control at the beginning and at the end of the study.Total HDL cholesterol, LDL cholesterol, and triglycerides, both initial and after one year.Initial and final weight. Initial height. Difference in body mass index (BMI) between the first and final visits.

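### Patients prescribed outside the active-ingredient rule are neither restricted nor identified, so doctor-selected patients may sit unseen in the non-exposed group

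*Protocol article*

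**What the plan says.** **How exposure arises.** The Background of the protocol article says that "the doctor writes the prescription according to the active ingredient, with some exceptions (therapeutic needs and lower cost"), and that "the final choice for the commercial brand is determined by the pharmacy based on the lowest-cost criteria". It also cites a 2012 law that "requires dispensing the lowest priced drug out of all the pharmaceutical bio-equivalent presentations". The pharmacy change under study therefore arises mainly from prescriptions written by active ingredient.

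**Who is enrolled.** The Patients section states: "The patient must be under treatment with at least one of the following drugs: enalapril, amlodipine, and simvastatin", with a stable dose and consent. Its exclusions concern language, a foreseen move and severe disease or other limits on attendance. The Sampling section describes the same frame: age, "HTN and/or dyslipidemia, and treated with any of the 3 studied drugs". Neither section mentions how the drug is prescribed.

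**How the groups are formed.** The Sample size section contrasts "the exposed group (drug changes at the pharmacy) and the non-exposed group". The variable list records whether the presentation changed at the pharmacy (yes or no) and the number of changes per drug.

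**What is recorded about the prescription.** The list has "Prescribed active ingredient: enalapril, amlodipine, or simvastatin". It does not have prescription by ingredient or by brand, nor a reason for an exception.

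**How confounding is handled.** Data analysis specifies a logistic model for the combined outcome, with covariates chosen by their association in the bivariate analysis. The Discussion concedes that the exposure cannot be randomised but does not mention this subgroup.

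**The concern.** A cohort comparison of changed with unchanged patients is most easily read if the unchanged could have been changed and, for reasons unrelated to their risk, were not. The protocol names a route by which some patients may be unchanged for another reason: their doctor prescribed outside the active-ingredient rule. If that decision rests on therapeutic need, it is a clinical judgement about the patient and may be related to the risk of error or poor adherence. The Background itself notes that older patients with visual or cognitive deficits find presentation changes harder.

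The decision is the prescribing doctor's, and under Data collection the patient's own doctor is also the study researcher who recruits and records. This is a possible case of confounding by indication in the main comparison. With the variables as listed, the analysis could neither adjust for it nor show how large it is. Prescription mode for each interval may also be harder to reconstruct after the study than to note at each visit.

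**Working it through.** **Set the sections side by side.**

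1. The Background recognises a class of prescriptions outside the rule that gives the pharmacy its choice.
2. Patients and Sampling admit that class.
3. Sample size and the variable list assign exposure by whether a change occurred, so an unchanged member of the class is non-exposed.
4. The variable list does not identify the class, so the model in Data analysis cannot separate it.

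**Inputs for the size.** The plan gives no figure for the frequency of exceptions or for the adherence of these patients, so there is none to reproduce.

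- From Sample size: adherence 50%, taken as a failure risk of 0.50 in non-exposed patients open to pharmacy choice; odds ratio 2; 240 patients before the allowance for losses.
- Exposed risk: odds of 2 × (0.50/0.50) = 2, so 2/3 = 0.667.
- Assumed: the share *f* of non-exposed patients under an exception runs from 5% to 30%, and their failure risk *r* from 0.30 to 0.70.

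**Formulas.** Non-exposed risk p = 0.50(1 − f) + r·f. Apparent odds ratio = 2(1 − p)/p when the true value is 2, and (1 − p)/p when the true value is 1.

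| f | r | p | Apparent OR, truth 2 | Apparent OR, truth 1 |
|---|---|---|---|---|
| 5% | 0.30 | 0.49 | 2.08 | 1.04 |
| 5% | 0.70 | 0.51 | 1.92 | 0.96 |
| 10% | 0.30 | 0.48 | 2.17 | 1.08 |
| 10% | 0.70 | 0.52 | 1.85 | 0.92 |
| 20% | 0.30 | 0.46 | 2.35 | 1.17 |
| 20% | 0.70 | 0.54 | 1.70 | 0.85 |
| 30% | 0.30 | 0.44 | 2.55 | 1.27 |
| 30% | 0.70 | 0.56 | 1.57 | 0.79 |
| any | 0.50 | 0.50 | 2.00 | 1.00 |

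Example: f = 30%, r = 0.70 gives p = 0.35 + 0.21 = 0.56, and 2 × 0.44/0.56 = 1.57.

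**Power cost of a restricted comparison.** Assume a two-sided test at 0.05, an equal split of 240 and independent patients; the plan states neither the sidedness nor the split. Power = Φ[(0.1667 − 1.96·SE₀)/SE₁], where SE₀ uses the pooled risk and SE₁ the two separate risks.

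- Nobody removed (120 and 120): SE₀ = 0.0637, SE₁ = 0.0627, power 74.8%.
- 10% of the non-exposed removed (108 and 120): pooled risk (54 + 80)/228 = 0.588, SE₀ = 0.0653, SE₁ = 0.0646, power 72.6%, a loss of 2.2 points.
- By the same formula, 5%, 20% and 30% removed (114, 96 and 84 against 120) give 73.7%, 69.9% and 66.7%.

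The starting value is below the planned 80% because two-sided testing of 0.50 against 0.667 with equal groups needs 274 patients. The stated 237 is approached (238) with a one-sided test and continuity correction. The point made here does not depend on that.

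**The case against.** The strongest reply is that much of the mechanism is inferred.

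**That exception patients cannot be switched.** A reader might infer this. The Background does not say so, and the cited law's lowest-price dispensing rule is described without linking it to the exceptions. A patient may also take up to three study drugs and be changed on another. What stands is weaker: on a natural reading, such prescriptions are largely outside pharmacy choice.

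**That all exceptions select on patient risk.** They do not. Lower cost is the other named ground and is not a judgement about risk. No section says what counts as therapeutic need.

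**That the bias hides harm from switching.** This is tempting if one pictures frail patients being protected from changes. It requires these patients to do worse than the other non-exposed, and nothing in the documents says so. With a lower risk the bias runs the other way. A calculation using only the 70% risk would show one side, and at that value they do worse than the 66.7% assumed for changed patients.

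**That an error followed by an exception reverses cause and effect.** For the yes/no exposure, a patient already changed stays exposed. Only the number of changes, or an error before any change, could be affected.

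**That a condensed article may leave this to the full protocol.** This has some force: there is an electronic data notebook and a review of the clinical record, and either could hold prescription mode. But eligibility, sampling frame, exposure and prescription variables are all set out here, and as set out they leave the subgroup inside the comparator and unidentified. The general admission in the Discussion that exposure is not randomised does not cover it.

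**Conclusion.** The point holds as a gap in design and data collection, not as a demonstrated bias. The protocol acknowledges prescribing exceptions, enrols patients regardless of them, counts the unchanged ones as non-exposed, and lists no variable to tell them apart. Where the exception rests on therapeutic need, confounding of the main comparison is credible.

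Its size and direction are unknown. At a true odds ratio of 2 the apparent value is about 1.6 to 2.6 over the assumed ranges. At a true value of 1 it is about 0.79 to 1.27. There is no distortion if these patients carry the same risk as the other non-exposed. The ranges rest on assumed shares and risks and on a 50% failure risk taken from the adherence figure alone, whereas the outcome also counts usage errors.

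**What to change.** 1. **Secondary outcome variables.** Add, per study drug: prescribed by active ingredient or by brand, and the reason for any exception (therapeutic need or lower cost). Take it from the clinical record at visit 1 and at each later visit. If the data notebook already holds this item, list it.
2. **Data analysis.** Prespecify the exposed versus non-exposed comparison restricted to patients whose study drugs are all prescribed by active ingredient at visit 1, and report it beside the full-sample result. Recording the item alone is not enough, because covariates enter the model only if associated with the outcome in the bivariate step.
3. **Later moves to an exception.** Do not end follow-up when a drug moves. If the move follows an error, that would be informative censoring. An analysis by drug and interval would also not fit the single patient-level combined outcome. Describe such moves and their timing relative to the first error.

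**Cost.** One more item per visit from a record already reviewed, and slightly lower power in the restricted analysis: about 2 points at a 10% share and about 8 at 30% (74.8% to 66.7%), if only non-exposed patients drop out. Changed patients with another drug under an exception would drop out too, so the loss could be somewhat larger. Full-sample power is unaffected, and prescribing is unchanged.
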